### 3.7.3 Qualitative data collection

The focus groups will last approximately two hours and the individual semi-structured interviews will last approximately one hour. Separate topic guides will be used for the focus groups and interviews with patients, service providers and key stakeholders (see Annexes 2 a-d for draft topic guides). These topic guides have been adapted to the context by the principal investigator who has experience of working in NCD clinics with Syrian refugees in Jordan and in other contexts. The included topic guides are indicative only; they will be further refined based on findings from the focus groups and from two pre-test interviews, which will be conducted to improve internal validity. The finalised topic guide will seek to provide guidance and structure to the interviews but not to restrict the discussion. They will be translated into Arabic and back translated into English.

The focus group and individual interviews with NCD patients, and interviews with key health staff are expected to take approximately 4 weeks, and will take place in August 2017. Training will be provided to the local researchers who will facilitate the focus groups and conduct interviews with NCD patients and some health care staff.

The focus group and interviews will be conducted either at the MSF clinics or office, or by telephone or Skype for expatriate workers who have left Irbid. The focus groups and interviews with NCD patients will be conducted in Arabic by either a male or female fluent Arabic speaker as appropriate (the local MSF research coordinator and one additional trained local interviewer). The non-Arabic speaking principal investigator will be present as moderator during the focus group discussions and will require a translator. Both focus group discussions and individual interviews will be audio recorded, typed as transcriptions in Arabic and then translated into English. The interviews with health staff will be conducted in Arabic by the local MSF research coordinator or English by the principal investigator, as appropriate, and audio recorded where possible (unless conducted by telephone or Skype where notes will be used instead).

Key stakeholder interviews will be informal and will last approximately one hour. They will be conducted in Arabic by the local research coordinator or in English by the principal investigator, as appropriate, and will take place at a location convenient to the interviewee e.g. MoH office either in person or via Skype and will be audio-recorded.

Participant observation will be conducted by the principal investigator with a translator. It will include observation of working practices, health education and group counselling sessions (including use of MSF OCA clinical guidelines, data recording interaction between staff and patients, and patient participation). Clinic layout, organisation, staffing level, staff time expenditure and patient flow will also be observed. Field notes will be taken and transcribed into a password-protected computer record. These will be triangulated with other data sources including data from FGD and SSIs and costing data.

The qualitative research will be led by an expatriate qualitative researcher (the principal investigator) who will help finalise the study design and instruments, be involved in the focus groups and interviews, undertake the participant observation and lead the analysis and write-up of outputs. This will be conducted in collaboration with a local research coordinator from within the MSF field team. [name] and [name] (LSHTM) will provide advisory support.

### 3.7.4 Quality assurance

The quality of the interviews will be assured in the following ways: First, the interviews will be led by researchers (i.e. PI and the local MSF research coordinator) who are experienced in qualitative research methods. Second, the interview topic guides will be developed following a rigorous process of expert consultation, group discussions and pre-testing to ensure relevance, reliability, and appropriateness. Third, the quality of the data transcription and translation will be assured through random checks and discussions with key staff involved in the data collection. Experienced transcribers and translators will also be used, and training given to them on the research to ensure familiarity with key terms and concepts. Fourth, the data analysis methods and use of specialist coding software (NVivo) will support transparency and reliability in the analytical decision-making (see below). This will be supported through triangulation (e.g. with other data sources) and peer review and discussion. Fifth, a limitations section will be included in any project outputs to clarify limitations in the study. Sixth, regular meetings will be held between the researchers to discuss and maintain quality assurance. Finally, the qualitative research will be underpinned by agreed principles of good practice including transparency, comprehensiveness, reflexivity, ethical practice, being systematic.

### 3.7.5 Qualitative data analysis

A priori themes based on the NCD literature will be identified and included in topic guides (Annexes 2 a-d). A computer-assisted qualitative data analysis software package, NVivo 11 (QSR International), will be used to manage the qualitative data. Thematic analysis, using a positivist approach, will be utilised to detect key emerging themes arising from the data, while using the overall RE-AIM framework to help structure it. Where appropriate, the qualitative data will also be compared and contrasted with the other data sources, including quantitative data from the cohort study and costing data, to triangulate study findings.

Figure 1 Irbid NCD Evaluation Summary of Methodologies and Indicators (reproduced and adapted from De Silva *et al* ^30^)

# 4. Ethical considerations

## 4.1 Social value

Potential patient benefits from the cohort include improved continuity and quality of NCD care and reduced risk of acute and chronic complications. Community-level benefits include access to improved NCD care in Irbid governorate. Potential programme benefits include provision of new information to help understand the strengths and weaknesses of the NCD service and its potential for use in other settings. The study team will ensure that any changes to NCD programming and operations suggested by this research are implemented within MSF projects in Jordan, in the wider Syrian refugee context and elsewhere; and that the findings inform planning for subsequent NCD interventions within MSF programmes.

There is currently a lack of evidence regarding the delivery of NCD interventions in crisis settings, particularly on longer-term outcomes. National and international level benefits of this evaluation include adding to the broader knowledge base by identifying implementation bottlenecks; exploring programme feasibility, cost and use of a setting-specific guideline; and identifying future research questions. Findings from this study will be available to the Jordanian MoH, NGOs and other relevant actors who are involved in the planning and implementation of similar programmes.

## 4.2 Potential risks from the study

The focus groups could discuss emotional challenges of having NCDs, which could possibly cause distress. Overall, these risk are expected to be low and the programme has experienced psychosocial workers to respond to any participant distress. The local qualitative research coordinator will receive training in interview technique, specific briefing on refugee mental health and debriefing post-interviews. Our previous experience of conducting interviews on this topic at the MSF hospital in Mweso in DRC did not report any cases of distressed respondents.

## 4.3 Respect for and protection of recruited participants and study communities

Acknowledging the time burden and potential direct and indirect costs that focus group discussion and interview participants may incur, the study will provide transport costs and refreshments during the process. Interview participants will be able to select a time convenient to them to minimise potential loss of earnings.

Prior to the study, the research team will meet with Ministry of Health co-investigators and other relevant staff to discuss the study with them (including its aims, objectives, methods and process) and gain their support for the study. The Jordanian and broader research community will be engaged through presentations at conferences, scientific meetings and through scientific publication.  In addition, local medical staff members will gain research skills through their contribution to this evaluation.

The Irbid NCD programme initiated a community engagement strategy in early 2017.  Syrian refugee community leaders were identified during the MSF Syrian refugee household survey conducted in 2016 and through the new outreach activities. These community leaders will be invited to an interactive meeting in advance of the focus groups discussions and individual interviews. Their opinions and concerns will be elicited and will inform the topic guides used. The community leaders will also be invited to participate in key stakeholder interviews.

## 4.4 Informed consent

Since the cohort study is based on analysis of routine patient data it will not involve any additional procedures and patients in the cohort study will not be asked to give written consent for use of their routine data. However, information sheets on the walls of the clinic will inform patients about the study.

For the completed MSF cross-sectional household survey, written informed consent was obtained prior to the beginning of each interview. For illiterate individuals or in case the interviewee agreed to conduct the interview but did not want to sign, verbal consent was obtained and testified by the data collectors. Further, for every subsection, which interviewed different members of the household, verbal consent was obtained and recorded individually for every section.

Participants in the qualitative study and medication adherence survey will be asked to give written consent to participate. If the individual’s literacy is limited, they can give verbal consent provided that a witness who is appointed by that individual can sign the consent form on their behalf. For the participant observation component of the study, participants will receive the information sheet; they will be asked to give verbal consent and they will be advised they can opt out of participating at any time without repercussion.

For securing written consent from former health care workers who are no longer working in Irbid and who will be interviewed telephonically or via Skype, the information sheet and consent form will be emailed to them in advance of the interview, and written consent sought through email confirmation. Verbal consent will also be sought prior to the telephone/Skype interview.

The contents of the information sheet and consent form are given in Annex 1. These contain key elements related to: the purpose of the study and qualitative methods; the process and summary content of the interviews; the respondent selection process, the potential harms from the study; and clarification that the potential benefits from the study will be for knowledge and clinical practice generally, and not for the participants own health status (in order to avoid therapeutic misconception); the risk of residual disclosure, the ability to pause or stop at any point, confidentiality, anonymity, and freedom of consent.

## 4.5 Safety considerations

To address any inappropriate or harmful prescribing potentially identified during the evaluation, the patient will be informed, the error corrected and any identified harm treated as appropriate. In addition, a comprehensive audit will be undertaken to identify and remedy similar errors and refresher training sessions undertaken with staff.

To avoid therapeutic misconception, the written information sheets and verbal information will make it extremely clear that participation in the research will have no influence on the treatment received or clinical outcomes (see Information Sheet in Annex 1).

To avoid the risk of residual disclosure in focus group discussions, interviewers will not be aware of participants’ specific disease status and so will not be able to accidentally disclose it or give out information for other participants to be able to deduce the stats of fellow participants. Participants will also be reminded about the risk of residual disclosure in the information sheet and verbal introduction prior to the focus group.

To avoid NCD clinic healthcare worker respondents interpreting the interviews as an evaluation of their individual performance in the clinics (especially as this study evaluates the NCD service), briefings will be made with all clinic health care workers explaining that: an independent researcher from LSHTM will perform the majority of the interviews; data will anonymised before reporting; and gaps identified will be addressed in a general training session for all staff. This will be reiterated in the written information sheet and verbal information provided.

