### 3.7.2 Qualitative research study population and sampling

Information about the study will be provided to all patients attending both MSF NCD clinics in Irbid using posters and leaflets and discussion during group education and counselling sessions. Two same-sex focus groups of approximately eight people each will be conducted with a cross-section of NCD outpatients, aged 18 or above, including a mix of patients attending either of the two MSF clinics. Patient selection will be based on NCD type and severity, age, gender and literacy as suggested by MSF clinical staff.

These focus groups will be followed by individual semi-structured interviews. Some participants of the focus groups who had particularly insightful perspectives will be purposively selected for individual interviews by the principal investigator and local study coordinator in order to follow-up on key issues raised. Specific permission to re-contact focus group participants and the right to withdraw this consent will be included in consent forms. The research coordinator will separately record the participant’s preferred means of contact to protect their confidentiality.

Patients attending either clinic will be approached in the waiting room by the local research coordinator, informed about the study and invited to participate in focus groups and /or individual interviews. Approximately 12 or more individual interviews with NCD patients recruited from both clinic sites will be conducted, aiming to include patients who have accessed each component of the NCD service (including HLO, home visit service, MHPSS). This is subject to principles of saturation.

Approximately 12 semi-structured interviews will be conducted with key staff involved in the provision of NCD care in either of the two MSF clinics. These staff will be purposively selected to reflect the range of activities and staff functions involved. They may include the doctors and nurses, psychosocial workers, field co-ordinator, and expatriate MSF medical and research staff in Irbid and internationally either currently or previously involved in the NCD programme. Participants will be eligible if they are full-time members of staff (i.e. not temporary workers) and have worked in the NCD clinic, in the MSF Irbid NCD project office or as MSF Jordan country coordination or headquarters staff from December 2014 to the present for a minimum of three months.

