# Annex 2: Data collection forms

## Annex 2a: Topic guide – Focus group discussions with NCD patients

| Key area | Themes | Question |
| --- | --- | --- |
| Introduction | Study aim and agencies involved | Why invited to participate? Consent & any questions? |
| Participant Background | Getting to know each other + building rapport | Could you tell us a bit about yourself? *Prompt: e.g. profession, what area live in, when you were first diagnosed with [NCD condition]?* |
| Reach | Access  Barriers to accessing care for NCDs  Ways of reducing barriers | What do you know about your NCD condition(s)? *Prompt – e.g. causes, types, who gets it, treatment*  Could you tell me about how you came to learn about your NCD condition(s)? ? *Prompt – e.g. from friends/family, from the radio (or other media), when diagnosed at hospital.*  What were you told about NCD condition(s) when you were enrolled in the MSF clinic? *Prompt – probe understanding of NCD condition(s) such as causes, risks and its management (medication and diet).*  What do you think might prevent people from attending this service for their NCD condition(s)? *Prompt: lack of knowledge, lack of services, costs, time, quality of services, stigma etc.*  How could access to healthcare for NCD condition(s) be improved? |

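### Section 4.5 says focus-group interviewers will not know participants' specific disease, but the Annex 2a group guide prompts for it in front of the group

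*Protocol*

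**What the plan says.** Section 4.5 (Safety considerations) names residual disclosure as a risk of the focus groups and gives the means of avoiding it: "To avoid the risk of residual disclosure in focus group discussions, interviewers will not be aware of participants"' specific disease status, and on that ground cannot reveal it by accident. It adds that interviewers will therefore be unable to let slip anything from which others could work the status out. The following sentence promises a reminder of the same risk in the information sheet and in the spoken introduction to the group.

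Three other places bear on this:

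- **Section 3.7.2 (sampling).** "Patient selection will be based on NCD type and severity, age, gender and literacy as suggested by MSF clinical staff". On recruitment: "Patients attending either clinic will be approached in the waiting room by the local research coordinator".
- **Section 3.7.3 (data collection).** The groups are run by an Arabic speaker of the appropriate sex, drawn from "the local MSF research coordinator and one additional trained local interviewer". In addition, "The non-Arabic speaking principal investigator will be present as moderator during the focus group discussions", with a translator.
- **Annex 2a (focus-group guide).** The background item invites people to introduce themselves, with a prompt that includes "when you were first diagnosed with [NCD condition"]. The Reach block opens with "What do you know about your NCD condition(s"). Later items ask what the person was told on enrolment, how they manage the condition at home, and what has made keeping up their treatment difficult.

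**The concern.** Section 4.5 makes interviewer unawareness the mechanism of protection, while the guide used in the same sessions asks for the information that the interviewer is supposed to lack. Anyone who relies on section 4.5, an ethics board included, would credit the focus groups with a protection that the rest of the protocol does not deliver.

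At stake are participants' privacy about which condition they have and, secondarily, the frankness of what they say. Annex 2a itself lists stigma and shame among its prompts, so the authors regard the subject as sensitive.

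**Working it through.** No arithmetic applies beyond the head count, so the check sets the texts side by side.

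**Step 1. What is promised.** Section 4.5 concerns the specific disease. Attending an NCD clinic is already known to everyone in the room; the particular diagnosis is not. The promise has two parts: interviewers do not know the diagnosis, and so they cannot reveal it.

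**Step 2. The group guide.** Take the Annex 2a items in order.

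| Annex 2a item | What an ordinary answer reveals |
| --- | --- |
| Background prompt on date of first diagnosis, with a slot for the condition | The condition, if the slot is filled or the answer names it |
| Reach: knowledge of own condition, prompted on causes, types and treatment | Usually the condition |
| Adoption and implementation: information on managing it, self-management at home | Often the condition, through medicines or diet |
| Maintenance: difficulty in keeping up own medical treatment | Often the condition or its treatment |

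The first row is the clearest. It solicits a fact about the person's own diagnosis, as part of the introductions. From then on the interviewer, the moderator, the translator and the other participants may all know it. The first part of the promise fails when the guide is used as written. The documents contain this contradiction explicitly, and it does not depend on how patients were recruited.

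**Step 3. Recruitment.** Section 3.7.2 selects on NCD type and severity as clinical staff suggest, and the local research coordinator approaches patients. Section 3.7.3 names the same coordinator among those who conduct the groups. For unawareness to hold at the start of a session, the suggestion of names must reach the coordinator without diagnoses attached. The protocol neither says that it does nor that it does not. Clinical staff hold the diagnoses and could select on them without passing them on. This step therefore shows a gap in description and no contradiction. Because the groups are same-sex and the facilitator is matched to the group, the coordinator may also run only one of the two.

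**Step 4. What remains.** Section 4.5 keeps the reminder of disclosure risk. Section 4.4 lists residual disclosure and the freedom to pause or stop among the consent contents. Section 4.7 has participants agree to keep the discussion confidential. None of these makes interviewers unaware, but each bears on the risk itself.

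**Step 5. Size.** Two groups of about eight: 2 × 8 = 16 people, approximately. No outcome, estimate or sample size in the cohort, audit or adherence survey is involved.

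**The case against.** The best reply is that section 4.5 is narrower than it looks. It guards against an interviewer letting something slip; it does not promise that participants will keep silent about their own illness. A participant who answers a question about diagnosis has spoken for themselves, and the reminder and the confidentiality request address that risk. The guide is also a draft to be refined after pre-testing, the diagnosis prompt is one example among several, and its condition slot is left unfilled.

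Much of this stands. The aim of section 4.5 is accidental disclosure by interviewers, and once a participant has named a condition aloud the interviewer has little left to reveal to that group. But the sentence states as fact that interviewers will not know, and the guide supplied with the protocol has them ask. Draft status makes the repair easy; it does not reconcile the two texts.

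A reader might go further than the documents allow, in four ways:

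- **That the focus groups have no protection.** They do: the measures in sections 4.4, 4.5 and 4.7 listed under step 4. Only interviewer unawareness fails.
- **That the coordinator knows each diagnosis from recruitment.** The protocol never says that diagnoses are handed over.
- **That participants are misled.** The consent forms are not in the text available. What sections 4.4 and 4.5 show is that participants are warned of the risk; nothing shows they are told that interviewers will be unaware of their disease.
- **That neighbours or acquaintances will be in the group.** The protocol does not describe the groups in that way.

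**Conclusion.** The point holds in a limited form. As written, section 4.5 and Annex 2a cannot both be followed: the guide prompts, in the group, for the disease information that interviewers are said not to have. Recruitment leaves it unclear whether they are unaware even beforehand.

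The conclusion assumes that the final group guide resembles the one in Annex 2a; if pre-testing removes the diagnosis prompt, the sharpest part of the conflict goes with it. The matter concerns about 16 people and is one of ethics and conduct. It is minor, has no bearing on any analysis, and is worth correcting because the correction is so small.

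**What to change.** Make three edits:

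1. **Annex 2a.** Delete the own-diagnosis example from the prompt in the background item. The same prompt already stands in Annex 2b, for individual interviews that section 4.7 places in a private space, so no information is lost.
2. **Section 3.7.2.** Add one sentence: clinical staff select on NCD type and severity and give the coordinator the list of suggested patients without diagnoses.
3. **Section 4.5.** Replace the claim of unawareness with a statement that interviewers are not given disease status beforehand but may learn it from what participants choose to say, and that the reminder and the confidentiality request cover this.

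The other group questions can stay. Section 3.7.1 wants participants' own experience of benefits, barriers and acceptability, and rewording every item to people in general would weaken that for a debatable gain.

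The cost is one deletion and two sentences, best done before the guide is translated and back-translated. No change to sample, schedule or analysis is needed.
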